**Methods/design:**

The trial is designed as a two arms, parallel-group, open-label randomized controlled intervention study. The Log-rank Test was used for calculating sample size based on the latest national multicenter survey data of DFU in China. Three hundred and twenty participants will be recruited from the Diabetic Foot Care Center, West China Hospital, Sichuan University. Adults with diabetic peripheral neuropathy, healed foot ulceration in the 3 months prior to randomization, and aged ≥18 years, will be recruited. Participants will be randomized to receive novel diabetic therapeutic footwear (*n* = 160) or their own footwear (*n* = 160). The primary outcome will be the incidence of ulcer recurrence. The secondary outcome will be measurements of barefoot dynamic plantar pressures, the influence of footwear adherence on ulcer recurrence, and the incidence of cardiovascular events. Assessment visits and data collection will be obtained at baseline, 1, 3, 6, 9, and 12 months. The intention-to-treat principle will be applied. A cox regression model will be used to calculate the hazard ratio for the incidence of ulcer recurrence. The change of barefoot dynamic plantar pressures will be assessed using repeated measures ANOVA. The study protocol has been approved by the Ethics Committee of The Biomedical Research Ethics Committee of West China Hospital, Sichuan University (Reference No. 2019(96)).

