### Sample size calculation

PASS 11.0 software was used to obtain sample size. As a parallel-group randomized controlled trial, the Log-rank Test (Lakatos) was used for the sample size calculation based on the following parameters or assumptions:
The survival probability of treatment group was estimated for 77.9%. According to the latest national multicenter survey data in China, 31.6% patients with a history of DFU developed new ulcer during 1 year follow-up [5]. Thus, the survival probability of control group was assumed to be 64.8%. We assume that the treatment group could have a 30% higher survival probability than control group.The accrual period for patients’ recruitment was estimated for 12 months. The accrual pattern would be equal. The follow-up period would be 12 months. Therefore, the total time of this trial would last 24 months.The power was set at > 0.8, while *α* was 0.05. The dropout rate of 0.2 was assumed. No switching between two groups. Two groups would have same sample size.

Therefore, the total sample size calculated using PASS was at least 314 cases. In this trial, we would recruit a total of 320 patients (160 for each group).

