#### Secondary outcome measures

The secondary outcome measures include (1) the change of barefoot dynamic plantar pressures, from the third to the sixth diaries compared with that from the first diary (screening period); (2) the influence of footwear adherence on ulcer recurrence; and (3) the incidence of cardiovascular events.

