### Statistical analysis

At the end of this trial, all original data without participants’ name and the random sequences will be sent to a statistician for data analysis. Statistical analysis will be performed using SAS version 9.4 (SAS Institute Inc., Cary, NC, USA). Significance level will be set at *α* = 0.05. Quantitative variables expressed as means ± standard deviation or median with interquartile range, and categorical data will be recorded as numbers and percentages. Between-group differences of continuous variables will be tested for significance using Student *t* test when original data or data via transformation of variables is normally distributed or using Wilcoxon rank-sum test when data is not normally distributed. A chi-square test will be used for categorical data.

The primary end point, ulcer recurrence, will be analyzed according to the intention-to-treat principle, with event curves for the time to the first event on the basis of Kaplan–Meier analysis, and treatments will be compared by means of the log-rank test. A cox regression model will be used to calculate the hazard ratio for the primary end point. Among secondary end points, plantar pressures at baseline and at 3, 6, 9, and 12 months will be compared with repeated measures ANOVA. The changes blood flow parameters of lower extremity at baseline and at 12 months will be compared using Student *t* test when these means between groups are comparable at baseline or using analysis of covariance (ANCOVA) when these means are not equivalent at baseline. For cardiovascular events, the hazard ratio for the comparison of treatment group with control group and 95% confidence intervals will be estimated with the use of a proportional-hazards model.

The footwear adherence will be calculated for each group and then ulcer recurrence rates will be compared between the subgroups of patients with high adherence and low adherence by *χ*^2^ tests. We also plan to explore whether potentially important covariates such as age, sex, body mass index, physical activity, and diabetic duration could potentially confound the results.

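### Blood flow: observed baseline balance picks the test, usually the less precise one; fix ANCOVA in advance, and fit plantar pressure with a baseline-adjusted model on all available visits

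*Protocol article*

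**What the plan says.** The Statistical analysis section sets two rules for continuous mechanism measures.

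- **Blood flow.** "The changes blood flow parameters of lower extremity at baseline and at 12 months will be compared using Student *t* test" is the first branch. The choice of branch then depends on the data: "when these means between groups are comparable at baseline or using analysis of covariance (ANCOVA) when these means are not equivalent at baseline". Nothing says how comparability is judged. The Baseline visit section names three parameters (maximum systolic, maximum diastolic and time-averaged mean velocity), so the rule could apply different tests to sibling measures in the same trial.
- **Plantar pressure.** "Among secondary end points, plantar pressures at baseline and at 3, 6, 9, and 12 months will be compared with repeated measures ANOVA". Baseline is one of five time points. No SAS procedure, covariance structure or rule for missed visits is named.

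Three other statements bear on this. The sample size section says "The dropout rate of 0.2 was assumed". The abstract says without restriction "The intention-to-treat principle will be applied", while the Statistical analysis section ties it to one end point: "The primary end point, ulcer recurrence, will be analyzed according to the intention-to-treat principle". The Follow-up visits section plans to collect plantar pressure from participants who drop out only where possible.

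**The concern.** Randomisation makes the arms comparable in expectation, so an observed baseline difference is chance. Letting that difference choose the test has no benefit over adjusting for baseline every time. When the arms look alike, the rule uses the change score, which is less precise than ANCOVA at any correlation below 1. When there is a moderate gap that still counts as comparable, the change score carries part of the gap into the effect estimate. Because no criterion is stated, the choice would also be made after the data are seen.

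For plantar pressure, the worry is that the named method, in its textbook form, needs every participant to have all five values and does not use baseline as a covariate. The Discussion relies on plantar pressure and blood-flow velocity to show that the footwear works as intended, so the precision of both matters to the trial's mechanistic claims.

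**Working it through.** The plan has no figure of its own to reproduce here. Its only sample size calculation is for the log-rank test on ulcer recurrence, and it gives no SD, correlation or power for blood flow.

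**1. Precision of the two blood-flow branches.** Let r be the correlation between baseline and 12 months (not in the documents; range assumed) and take equal variance at both times. In units of that variance, the change score has 2(1−r) and ANCOVA has 1−r². The ratio is (1−r²)/(2(1−r)) = (1+r)/2. The extra patients needed by the t test are 2/(1+r) − 1.

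| r | Change score | ANCOVA | Ratio | Extra patients for t test | Power of t test where ANCOVA has 80% |
|---|---|---|---|---|---|
| 0.3 | 1.40 | 0.91 | 0.65 | 54% | 62% |
| 0.5 | 1.00 | 0.75 | 0.75 | 33% | 68% |
| 0.7 | 0.60 | 0.51 | 0.85 | 18% | 73% |
| 0.9 | 0.20 | 0.19 | 0.95 | 5% | 78% |

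**2. Behaviour of the whole rule.** This used 20,000 simulated trials with no treatment effect and 128 per arm (160 less 20%). Comparable was taken as p > 0.05 on a baseline test, which is an assumption.

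| r | ANCOVA chosen | Type I error of rule | SE of rule / SE of ANCOVA | False rejection by change t test when baseline p is 0.05 to 0.30 |
|---|---|---|---|---|
| 0.3 | 5.1% | 0.041 | 0.1410/0.1197 = 1.18 | 8.9% |
| 0.5 | 4.6% | 0.042 | 0.1201/0.1076 = 1.12 | 7.4% |
| 0.7 | 5.2% | 0.046 | 0.0949/0.0894 = 1.06 | 7.2% |
| 0.9 | 4.9% | 0.050 | 0.0560/0.0549 = 1.02 | 5.7% |

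The t test is therefore used in about 95% of trials. Overall error is at or below 0.05; the excess in the last column is conditional on a moderate imbalance.

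**3. Uncorrected imbalance.** With no treatment effect, a baseline gap d leaves an expected 12-month gap of r·d, so the change score is shifted by (1−r)·d in the opposite direction. The largest gap that passes a 5% test with 160 per arm is 1.96 × √(2/160) = 0.219 SD. The shift is then 0.153, 0.110, 0.066 and 0.022 SD at r = 0.3, 0.5, 0.7 and 0.9. These are near-worst cases for trials on the t-test branch.

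**4. Plantar pressure, if complete cases are used.** 320 × 0.2 = 64 lost and 256 kept. The variance of a complete-case change contrast was compared with that of a baseline-adjusted model on all available data, with the 20% dropout spread evenly over the four follow-up visits and r from 0.5 to 0.9.

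- Missing data alone: variance 2% to 7% higher for month 12, and 12% to 14% higher for the average of the four visits.
- Missing data plus no baseline adjustment, month 12: 37%, 22% and 10% higher at r = 0.5, 0.7 and 0.9 with equal correlations between visits; 92%, 68% and 30% higher when r is the adjacent-visit correlation and decays with distance.

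Most of the loss at month 12 comes from leaving out the baseline covariate.

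**The case against.** The strongest reply is that the consequences are modest and partly unproven. Much of this stands.

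- A reader might infer that a data-dependent choice of test inflates false positives. It does not under the criterion assumed here; the rule is slightly conservative. The cost is precision and conditional bias.
- A reader might infer that repeated measures ANOVA will delete anyone who misses a visit. The protocol does not say so. Classical software routines do this, but a mixed-model fit of the same design keeps partial data, and a condensed article may leave the procedure to the analysis plan. Some drop-outs may also still be measured. The 64 is therefore conditional.
- A reader might infer a breach of intention-to-treat. The Statistical analysis section promises it for the primary end point only. A conflict arises only with the abstract's general sentence, and only if complete cases are used.
- A reader might object that a group main effect would average in the untreated baseline. The protocol does not name that contrast. The Secondary outcome measures section defines the outcome as change, for which the arm-by-time test is natural.
- A reader might assume that participants with a new ulcer would have no pressure data. The protocol schedules pressure every three months with no such exception.
- Blood flow is not among the outcomes that begin "The secondary outcome measures include (1) the change of barefoot dynamic plantar pressures". It is a mechanism measure, treated alongside the secondary end points only in the Statistical analysis section.
- At r = 0.9 the variance gain from ANCOVA is only 5%.

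What the reply does not remove is the blood-flow rule itself. It is written out in full, so it is not a detail left to another document, and it is never more precise than adjusting every time.

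**Conclusion.** The point holds for blood flow, at modest size. The stated rule is undefined at its decision step. Under a 5% baseline test it gives the less precise analysis in about 95% of trials, with ANCOVA variance 5% to 35% lower over r = 0.9 to 0.3. Overall type I error is not inflated. The size rests on the assumed r, on equal variances at the two times, and on the assumed criterion; a looser threshold for imbalance would send more trials to ANCOVA.

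For plantar pressure the point is conditional: up to about 64 of 320 participants dropped if the method is run on complete cases, and a loss of precision from not adjusting for baseline. The text does not support saying that the method deletes participants or breaks intention-to-treat. Neither part touches the log-rank and Cox analysis of ulcer recurrence or the target of 320.

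**What to change.** **Blood flow.** Replace the two-branch rule with one sentence: each 12-month parameter is analysed by ANCOVA on arm and baseline value, whatever the observed balance.

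**Plantar pressure.** Specify a linear mixed model (REML) on the 3, 6, 9 and 12 month values, with arm, visit, arm-by-visit and the baseline value as terms and an unstructured covariance. Use every available follow-up value and report the arm difference at 12 months. Participants with no follow-up value contribute nothing to this model, so report their number by arm, and state that it assumes data are missing at random.

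The Baseline visit section describes these measurements after the randomisation step, so the text should confirm that they are taken before the study footwear is worn.

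The cost is wording only. The baseline values are already collected, both models are standard in the SAS version named, and no sample size changes. The change should be made before outcome data are seen.

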## Objectives

The objectives of this trial are as follows:
To verify the efficacy of the therapeutic footwear with vibration chip and merino wool prevent ulcer in preventing ulcer recurrence among patients with a history of DFU.To determine whether the therapeutic footwear can reduce the plantar pressure among patients with a history of DFU.To examine whether patients wearing the therapeutic footwear have better feeling of comfort and higher footwear adherence and also assess the influence of patients’ footwear adherence on the efficacy of the therapeutic footwear.To examine whether patients wearing the diabetic footwear have fewer cardiovascular events than those wearing non-improved footwear.

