#### Follow-up visits

Participants will be followed at 1 month (visit 2), 3 months (visit 3), 6 months (visit 4), 9 months (visit 5), and 12 months (visit 6) after randomization. At each visit, the trial team will collect the information including incidence of foot ulcer, footwear adherence, cardiovascular events, glucose profile, and other cardiovascular risk factors control. For physical activity evaluation, participants will be asked to wear a pedometer (P084, SPORTWAY, ShenZhen, China) every day to record the date and steps taken per day. Meanwhile, a concealed activity monitor (Lifecorder Plus, Suzuken) will be attached to the diabetic therapeutic footwear. Activity data will be uploaded by a research assistant to a centralized server via internet at each follow-up visit. Adherence to treatment will be evaluated through the comparison of the step counts recorded by a concealed activity monitor with those recorded by a pedometer. Adherence to treatment will be monitored until the end of follow-up. Plantar pressure distribution patterns will be measured after randomization every 3 months. At the end of follow-up, ABI and blood flow parameters of lower extremities will also be collected. At each visit, if participants make a withdrawal request or are not eligible to continue due to the presence of severe concomitant diseases or conditions listed in the exclusion criteria, they will be discontinued from the study. For participants who drop out, the information including incidence of foot ulcer, footwear adherence, cardiovascular events, ABI (if possible), plantar pressures (if possible), and biochemical parameters (if possible) will be collected.

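### Adherence has no control-arm value on the stated step-count metric, and nothing limits it to wear before the first ulcer when recurrence is compared by adherence class

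*Protocol article*

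**What the plan says.** All references are to the protocol article.

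- **Metric (Follow-up visits):** "Adherence to treatment will be evaluated through the comparison of the step counts recorded by a concealed activity monitor with those recorded by a pedometer".
- **Where it is measured (same section):** "a concealed activity monitor (Lifecorder Plus, Suzuken) will be attached to the diabetic therapeutic footwear". Every participant is asked to wear a pedometer. No shoe monitor is described for the controls' own footwear, either here or under Control footwear.
- **Window (same section):** "Adherence to treatment will be monitored until the end of follow-up". Recurrence is not listed as a reason to discontinue. The stated reasons are a withdrawal request or being "not eligible to continue due to the presence of severe concomitant diseases or conditions listed in the exclusion criteria".
- **Analysis (Statistical analysis):** "The footwear adherence will be calculated for each group and then ulcer recurrence rates will be compared between the subgroups of patients". The subgroups are "patients with high adherence and low adherence by" chi-square tests. No cut-off and no exposure window are given.
- **Aims:** Objectives asks whether patients in the therapeutic footwear "have better feeling of comfort and higher footwear adherence". Secondary outcome measures lists the influence of adherence on recurrence.

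**The concern.** There are two separate problems.

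First, the measurement and the analysis do not match. A ratio that needs a shoe monitor is to be computed in both arms, but the monitor is described for one arm only. A comparative objective depends on it.

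Second, the exposure may include time after the outcome. Each patient gets one adherence class, and recurrence is then compared between classes. If wear after the ulcer enters the class and wear changes because of the ulcer, part of any association runs from recurrence to adherence.

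The stakes go beyond a descriptive table. Background and Discussion both offer adherence as a possible reason why earlier randomised trials found no benefit. A spurious adherence effect could be used to explain away a null primary result here.

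**Working it through.** **1. Can adherence be computed in each group?**

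Adherence compares shoe-monitor steps with pedometer steps; take it as the ratio of the two.

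- Footwear arm (160): both counts are described.
- Control arm (160): the pedometer count is described, the shoe-monitor count is not.

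So 160 of 320 participants have no numerator. This follows from the text without further assumptions.

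**2. Does post-ulcer wear bias the comparison by adherence class?**

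The article gives no figure of its own for this analysis, so there is none to reproduce. One input comes from Sample size calculation: the treatment-arm ulcer-free probability of 77.9%. This gives recurrence of 1 - 0.779 = 22.1%, or 160 x 0.221 = about 35 patients.

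The other inputs are assumptions:
- individual adherence a has mean 0.60 or 0.70 and SD 0.20, and is independent of ulcer time (no true effect);
- ulcer time t is exponential, with monthly rate -ln(0.779)/12 = 0.0208;
- after the ulcer the shoe's share of steps is multiplied by k;
- after the ulcer total steps are multiplied by g (1 or 0.5);
- the cut-off is the median or 0.80.

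If wear is counted over all 12 months, measured adherence in a patient who ulcerates at month t is

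[a t + k a g (12 - t)] / [t + g (12 - t)].

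Example with a = 0.70, t = 3, k = 0.5:
- g = 1: (2.10 + 0.35 x 9)/12 = 0.44.
- g = 0.5: (2.10 + 0.35 x 4.5)/7.5 = 0.49.
- With k = 1 the result is 0.70 whatever g is. Walking less in total does not lower the ratio; only a lower share in the shoe does.

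Rate of chi-square p < 0.05 with no true effect:

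| Shoe's share of steps after the ulcer | False-positive rate |
|---|---|
| unchanged | about 5% |
| down 10% | about 7-13% |
| down 25% | about 20-57% |
| down 50% | about 40-99% |
| wear stops | about 60-100% |
| any of these, pre-ulcer wear only | near 5% |

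The ranges cover mean adherence, cut-off and post-ulcer step count. They also move with the assumed shape of the adherence distribution:
- A run at mean 0.70 with a beta-shaped rather than a truncated normal distribution gave 40-79% for a 25% fall, with recurrence of 10-17% in the high class and 27-29% in the low class.
- The same run gave 90-99% for a 50% fall (5-12% against 28-36%).

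If steps drop to a quarter after the ulcer, the rates are lower. At mean 0.60, a 25% fall in share gave 16-45% once that case was included.

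**The case against.** **The window is inferred.** Monitoring to the end of follow-up describes data collection. The article does not say that wear is summed over 12 months or that post-ulcer wear enters the classification, and an analysis plan not shown could set the window. This stands. It makes the second problem an open risk rather than a stated error.

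**The bias needs a further fact.** The shoe's share of steps must fall after an ulcer, and the article does not say that it does. Some patients with a recurrence might also leave the study, because use of offloading walking aids is an exclusion condition and Follow-up visits discontinues patients who meet one. This stands too. A reader might infer that recurrence necessarily produces low adherence, that the analysis cannot give a valid answer, or that it will show a protective effect where there is none. The documents support none of these, and the simulated rate starts at the nominal 5%.

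**Controls may have other adherence data.** Follow-up visits lists footwear adherence among the items collected at each visit, without limiting it to one arm. A reader might therefore reject the first problem, or conversely infer that nothing at all is collected on controls. Neither follows: the item is listed, but the only measure described is the step comparison, which controls cannot have. An analysis plan cannot supply a count that is not collected.

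**Chi-square is merely crude.** For a secondary, non-randomised comparison that is fair, and the test alone is not the point. The planned exploration of covariates, however, does not address the timing of wear relative to the ulcer.

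**Conclusion.** The first part holds as a contradiction in the text. Adherence as defined cannot be calculated for the 160 controls, so Objectives, Follow-up visits and Statistical analysis must be reconciled.

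The second part holds conditionally. As written, the comparison does not confine adherence to wear before the first ulcer and is open to reverse causation. Its size depends on an unknown: there is no inflation if the shoe's share of steps is unchanged, a modest excess if it falls by 10%, and about 20-57% false positives if it falls by 25%, with more beyond that. These figures rest on 22.1% recurrence in 160 patients and on the assumed adherence distribution, cut-offs and step counts. The remedy does not depend on them, since pre-ulcer wear keeps the rate near 5% throughout. Adherence would remain a non-randomised exposure even then.

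**What to change.** 1. Restrict the adherence-recurrence analysis to the footwear arm. Compute adherence only from wear before the first ulcer or censoring.
2. Replace the chi-square test with adherence up to the previous visit as a time-updated covariate in the Cox model already planned for this endpoint. Adjust for the covariates the article names (age, sex, body mass index, physical activity and diabetic duration), taken at baseline, and label the result non-randomised. Ulcers before the month 1 visit have no earlier adherence value. At the assumed rate that is about 160 x (1 - 0.779^(1/12)) = 3 patients, so the analysis can start at month 1.
3. Delete the per-group wording and limit the adherence part of the third objective to a description in the footwear arm, unless a comparable control-arm measure is specified.

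Cost: wording only. Pedometer steps are recorded by date, and activity data are uploaded at each follow-up visit. The downside is that the between-arm adherence claim is dropped. The article places recruitment after its own publication, so the change could be made before enrolment.
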